#### Intervention effects

3.3.2

Two‐level multilevel modelling will be done using Proc Mixed with SAS software version 9.4. In the level‐1 model, outcomes will be modelled as a linear function of time (baseline, 4‐, 8‐ and 12‐weeks postintervention) to create growth trends. In the level‐2 model, the growth trends will be modelled as a linear function of arm (intervention vs. control). Models will be constructed for OEs, exercise intentions, subjective exercise and objective exercise. For OEs, each dimension will be modelled individually to determine if intervention effects differed between OE dimensions and the average of all dimensions will also be modelled. The level of significance will be set at 0.05, two‐tailed. Effect sizes will be calculated by dividing each beta coefficient by the square route or residual error variance for each outcome. This value is interpreted similar to Cohen's d in which a small effect is 0.2, a medium effect is 0.5 and a large effect is 0.8 (Cohen, 1988).

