Breast cancer survivors often do not recognize the potential of exercise to help manage late and long‐term effects (Hirschey, Docherty, Pan, & Lipkus, 2016). They have low OEs of exercise having an impact on recurrence and mortality risk (Karvinen & Vallance, 2015). In one study, only 30% of survivors said that they thought exercise may decrease recurrence risk (Hirschey, Docherty, et al., 2016). However, survivors are typically motivated to change behaviours they believe will improve their long‐term outcomes and quality of life (O'Neill et al., 2013). Thus, increasing OEs may be effective to motivate exercise among breast cancer survivors.

The theoretical framework guiding this study (Figure 1) is adapted from Bandura's self‐efficacy theory (Bandura, 1982); the theory proposes that exercise increases when people both expect desired outcomes will occur (i.e. have high exercises OEs) (Bandura, 2004; Hatchett et al., 2013; Rogers et al., 2009, 2013) and believe that they can perform exercise (i.e. have high exercise self‐efficacy) (Bandura, 2004; Loprinzi & Cardinal, 2013). In contrast to the many studies targeted to increase self‐efficacy, tested strategies to increase OEs are few. Therefore, this study focuses on increasing OEs. This framework is novel because multiple OE dimensions are considered, importance, certainty and accessibility. Prior interventions have simply informed participants about exercise benefits, thereby failing to address multiple OE dimensions (Hatchett et al., 2013; Rogers et al., 2009; Short, James, Girgis, D'Souza, & Plotnikoff, 2014). Conversely, this study is designed to target and increase all three OE dimensions, which in unison are hypothesized to increase exercise intentions (the most proximal predictor of behaviour) (Ajzen, 1991; Scholz, Keller, & Perren, 2009) and exercise. This approach may be more successful than previous attempts to increase exercise OEs.

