#### Sample size

3.2.2

Power analyses for mixed models were performed using the optimal design to estimate detectable effect sizes. The analyses revealed that the required sample sizes for detecting a small (δ = 0.20), medium (δ = 0.50) and large (δ = 0.80) effect size of change in OE importance, certainty and accessibility, with a power of 0.80, at a significance level of α = 0.05, are 944, 154 and 62 respectively. Due to the exploratory nature of this study, 60 patients will be recruited. This sample size will allow for examination of the strength and direction of intervention effects.

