## DISCUSSION

4

This protocol article details the components of Moving On and how it will be tested to determine feasibility and intervention effects. There are several strengths to this study. First, Moving On is guided by a theoretical framework that is centred around a significant predictor of behaviour change, OEs (Bandura, 2004). Theory‐guided exercise interventions are usually more effective than those not guided by theory (Bluethmann, Vernon, Gabriel, Murphy, & Bartholomew, 2015). Additionally, when interventions are guided by theory, the constructs can be measured and analyses conducted to understand how the intervention operates and impacts each construct. This information aids researchers in designing more effective future interventions. Another strength of this intervention is that the population, whom it is designed to benefit (i.e. breast cancer survivors), participated in the creation of the study. The experiential knowledge these women bring to the study strengthens the likelihood that study participants will retain information about exercise OEs contained in the Moving On booklet (Bell & Bell, 2013). Finally, Moving On is an intervention that does not require expensive equipment or additional staffing such as exercise trainers or nurses to provide motivational interviewing. If Moving On is effective, it can easily be distributed during a regular follow‐up clinic visit; thus, this study has broad dissemination potential.

The planned feasibility trial of Moving On will allow the research team to test study procedures including recruitment and the use of Fitbit^®^ and online measures for data collection. The trial will also elicit feedback about what participants do and do not find beneficial about the Moving On booklet. The strength and direction of intervention effects on OEs and exercise will be identified. This information will facilitate refinement of Moving On materials and procedures in preparation for a future larger study.

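### Separate models for each outcome-expectation dimension are said to show whether effects differ between dimensions, but nothing in the plan tests or estimates that difference

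*Protocol article*

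**What the plan says.** Section 3.3.2 (Intervention effects) describes a two-level growth model for each outcome, in which the linear trend over baseline, 4, 8 and 12 weeks is regressed on arm. For OEs it states that "each dimension will be modelled individually to determine if intervention effects differed between OE dimensions", and it adds a further model for the average of the dimensions. The test level is given once: "The level of significance will be set at 0.05, two‐tailed". A standardised effect size follows: "Effect sizes will be calculated by dividing each beta coefficient by the square route or residual error variance for each outcome". It is read against 0.2, 0.5 and 0.8 as small, medium and large.

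The hypothesis at the end of section 2 (Background) is narrower. It says that each of importance, certainty and accessibility will rise more than in the control arm, and it says nothing about one dimension rising more than another. The dimensions still carry weight in the article: "This framework is novel because multiple OE dimensions are considered, importance, certainty and accessibility".

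**The concern.** The clause in section 3.3.2 joins a question to a method, and the two do not match. The question is whether the three arm effects are equal. The method tests three other null hypotheses, each that the arm effect on one dimension is zero. A significant result for certainty and a non-significant one for accessibility does not show that the two effects differ.

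Section 3.2.4 ties parts of the booklet to dimensions: the narratives mainly to certainty, one writing section to importance and another to accessibility. A statement that the booklet moved one dimension and not another therefore reads as a statement about which part worked. Section 4 says of the trial's findings that "This information will facilitate refinement of Moving On materials and procedures in preparation for a future larger study", so a misleading statement of this kind could feed into the next version.

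**Working it through.** **1. What each planned output can show**

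- *Model for one dimension:* whether that arm effect is zero.
- *Model for the average:* whether the mean of the three effects is zero. It says nothing about their spread.
- *Effect size for each outcome:* a point estimate scaled by that outcome's own residual SD. No standard error or interval for a difference is described.

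For two dimension effects with equal variance V and correlation ρ, Var(b1 − b2) = 2V(1 − ρ). The standard error of the difference is thus 1.18, 1.00, 0.77 or 0.45 times that of one effect at ρ = 0.3, 0.5, 0.7 or 0.9. Taking ρ as zero gives 1.41 times. Separate models do not estimate ρ, although all three dimensions rate the same 20 items in the same women (section 3.2.6).

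**2. The plan's own figures**

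For δ = 0.20, 0.50 and 0.80, section 3.2.2 gives total sample sizes that, "with a power of 0.80, at a significance level of α = 0.05, are 944, 154 and 62 respectively". It then says "60 patients will be recruited". A plain two-sample t calculation gives 788, 128 and 52. Multiplying the variance by f = 1.2 gives exactly 944, 154 and 62. That factor is back-fitted and not stated in the article, so it serves only to put the next step on the plan's scale. With 30 per arm and f = 1.2, power per dimension is about 11%, 41% and 80%.

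**3. Mixed verdicts when the three effects are equal**

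Mixed means that one or two of the three tests give p<0.05. If the dimensions were independent with power p each, P(mixed) = 1 − p³ − (1 − p)³:

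- p = 0.05: 1 − 0.0001 − 0.8574 = 14%
- p = 0.41: 1 − 0.069 − 0.205 = 73%
- p = 0.80: 1 − 0.512 − 0.008 = 48%

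Simulation (20,000 trials per cell, 30 per arm, f = 1.2) extends this to correlated dimensions. The article gives no correlation, so ρ is an assumption shown as a range.

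| True effect in all three | ρ=0 | 0.3 | 0.5 | 0.7 | 0.9 |
|---|---|---|---|---|---|
| 0 | 14% | 14% | 12% | 10% | 6% |
| 0.2 | 29% | 26% | 22% | 18% | 10% |
| 0.5 | 73% | 59% | 49% | 38% | 21% |
| 0.8 | 49% | 41% | 35% | 27% | 16% |

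A direct 2-df test that the three effects are equal rejects in 4.6% to 5.4% of trials in every cell.

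**4. A second parameterisation**

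Take 25 per arm (60 × 0.83 ≈ 50, from the 17% attrition limit in section 3.3.1). Take within-person correlation 0.69, the midpoint of the stated 4-week stability of .638 to .742. With visits at 0, 4, 8 and 12 weeks, the variance of a woman's slope scaled to 12 weeks is (144/80) × (1 − 0.69) = 1.8 × 0.31 = 0.558. For equal effects of 0.5, mixed verdicts occur in 57%, 47% and 36% of trials at ρ = 0.3, 0.5 and 0.7. With 30 per arm the range is 32-50%. With no effect it is 10-14%.

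This version is optimistic. It implies about 98.5% power at 0.8 with 31 per arm, where the plan states 80%, so its low mixed rate at 0.8 (8-11%) should not be relied on.

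**5. Reading the effect-size labels instead**

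In the step 3 set-up, three equal effects of 0.5 fall in different small/medium/large categories in 45% (ρ = 0.9) to 90% (ρ = 0) of trials. A true 0.5 lies on a category boundary, which inflates this. At a true effect of zero, away from any boundary, the figure is still 21% to 55%.

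**6. What a direct contrast could deliver**

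At N = 60 and f = 1.2, the standard error of one effect is √(1.2 × 2/30) = 0.283. The 95% half-width for a pairwise difference is then 1.96 × 0.283 × √(2(1 − ρ)), which is 0.66, 0.55 or 0.43 at ρ = 0.3, 0.5 or 0.7. In the optimistic set-up with 25 per arm and ρ of 0.3-0.7, power of the direct test is 21-43% for effects of 0.8/0.5/0.5 and 11-21% for 0.5/0.3/0.3.

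**The case against.** The strongest reply is that no decision rule is written. A reader might infer that a difference will be declared from the pattern of p-values, and that the plan will therefore report equal effects as different. The article does not say so. The percentages above apply only if that rule, or the effect-size labels, is used. This stands, and the rates must be stated as conditional.

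A reader might also infer that the separate models can give only a significant or non-significant verdict, so that unequal effects that all reach significance would pass as equal. That is not supported. The plan reports a standardised effect size for each outcome, and effects of 1.2 and 0.6 would be shown as different sizes. Those sizes remain descriptive, with no measure of uncertainty for their difference.

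Nor can a large gain in power be claimed for the direct test. With effects of 1.2/0.6/0.6 and the variance that matches the stated sample sizes, its power at 25 per arm is about 36-70% (ρ = 0.3-0.7), while mixed verdicts occur in 63-71% of trials. The case for the direct test is that it holds its 5% error rate and gives an interval.

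Finally, a reader might infer that booklet sections will be rewritten on these results. The article says only that the trial's information as a whole, including participant feedback and the fidelity questions, will guide refinement. The hypotheses in section 2 concern each dimension against control, and separate models suit them.

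None of this rescues the clause. It claims to determine a difference and names a method that cannot do so. It is a method stated in the text, so it cannot be treated as a detail left to an analysis plan.

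**Conclusion.** The point holds in a limited form: the stated method does not answer the stated question, and no planned output supplies a test or interval for a difference between dimensions. If a difference is read from significance, equal effects of 0.5 give a mixed verdict in roughly 35-60% of trials, falling to about 20% at a correlation of 0.9 and to 10-14% when there is no effect (correlation 0.3-0.7). A direct test gives about 5%. The size rests on an assumed reading rule, an assumed correlation range, and slope variances that are back-fitted or derived from the stability coefficients. The mismatch itself rests on none of these. What is at risk is a misleading statement about which dimension the booklet moves, within a secondary and exploratory aim. Recruitment, retention, Fitbit and fidelity conclusions are not affected.

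**What to change.** Keep the individual models for the hypotheses in section 2, and replace the clause about differences between dimensions with a direct contrast. Suggested wording:

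*Each dimension score will be standardised by its baseline SD. The three scores will be analysed in one mixed model with participant-level random intercepts and slopes correlated across dimensions. Differences in intervention effect between dimensions will be judged by the dimension × arm × time term and reported as pairwise differences with 95% confidence intervals. A significant result in one dimension and a non-significant result in another will not be taken as evidence of a difference.*

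If the joint model proves hard to fit with 50-60 women, fitting the existing growth model to the pairwise differences between standardised dimension scores addresses the same contrasts. A fully unstructured covariance over three dimensions and four visits should be avoided: it has 12 × 13/2 = 78 parameters.

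If the team does not want the comparison, the alternative is to delete the claim to determine a difference and report each effect with its interval.

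The cost is one changed sentence and one extra analysis in the same software, with no new data. The drawback is low power: at N=60 the contrasts will often be inconclusive for moderate differences, and the report should say so.

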##### Outcome Expectations

Outcome Expectations (OEs) will be measured using the multidimensional exercise OE measure for breast cancer survivors. This measure assesses the dimensions of accessibility, certainty and importance of 20 items that are possible outcomes of exercise specific to breast cancer survivors, such as decreased recurrence risk. The research team created and pilot tested this measure among a sample of 73 breast cancer survivors. The measure demonstrated excellent reliability (α 0.96–α 0.97) and stability over a 4‐week time period (*r*
_*s*_ = .638–.742).

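### The effect-size rule divides a growth-model slope by a within-person residual SD, so the result cannot be read on Cohen's d scale

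*Protocol article*

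**What the plan says.** All the relevant rules stand in section 3.3.2, Intervention effects, of the protocol article.

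- Level 1: "outcomes will be modelled as a linear function of time (baseline, 4‐, 8‐ and 12‐weeks postintervention) to create growth trends".
- Level 2: "In the level‐2 model, the growth trends will be modelled as a linear function of arm (intervention vs. control").
- Testing: "The level of significance will be set at 0.05, two‐tailed".
- Effect size: "Effect sizes will be calculated by dividing each beta coefficient by the square route or residual error variance for each outcome".
- Interpretation: the ratio is read in a similar way to Cohen's d, where "a small effect is 0.2, a medium effect is 0.5 and a large effect is 0.8".

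The section gives no unit of time, does not multiply the slope by the length of follow-up, and mentions no between-person SD.

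Two other places give the ratio its weight. The Sample size section (3.2.2) plans 60 patients, just below its own figure of 62 for a large effect, and justifies this by what the trial will show about the strength and direction of effects. The Discussion repeats the promise: "The strength and direction of intervention effects on OEs and exercise will be identified". It adds that the information gained will help refine materials and procedures ahead of a larger study.

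**The concern.** Cohen's d is a difference between groups, in outcome units, divided by the SD of that outcome between people. The stated ratio departs from this in two independent ways.

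**Numerator.** Because arm acts on the growth trend, the coefficient that carries the treatment effect is an arm-by-time slope: outcome units per unit of time. Its size depends on how time is coded.

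**Denominator.** In a two-level growth model the residual error variance is the level-1 part, the scatter of a person's own measurements around their own line. Stable differences between people go into the random effects. The residual SD is therefore smaller than the SD that Cohen's d uses.

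The first departure shrinks the number and the second inflates it. The two do not cancel in general, so the small, medium and large labels have no fixed meaning. At stake is the standardised measure of strength that this trial reports, and any use of it in preparing the larger study.

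**Working it through.** **Inputs from the article**
- Four time points: baseline, 4, 8 and 12 weeks (section 3.3.2).
- 4-week stability of the outcome-expectations measure: rank correlation .638 to .742 (section 3.2.6, Outcome Expectations).
- Planning effect sizes 0.20, 0.50 and 0.80 with total N of 944, 154 and 62, power 0.80, α = 0.05 (section 3.2.2).

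**Assumptions**
- The 4-week stability approximates the within-person correlation r.
- Compound symmetry holds, so total SD equals baseline SD.
- The formula is meant as coefficient ÷ √(residual variance).
- Baseline is time zero and the last visit is week 12.

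**1. The plan's own figures.** For a linear-growth comparison of two equal arms, use noncentral F(1, N−2) with

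λ = N·δ² / {4·[1 + (σ²/τ)/SS]},

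where τ is the slope variance, σ² the residual variance and SS the sum of squares of time. Four waves coded 0, 1, 2, 3 give SS = 5. With τ = σ² = 1 (assumed; not stated) the bracket is 1.2, and N = 944, 154 and 62, an exact match on all three. With the same variances, weekly coding gives 798, 130 and 52, and 0–1 coding gives 2200, 354 and 140. The planning figures are thus consistent with wave coding, though this is suggestive and not proof.

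**2. Numerator.** If time t is replaced by k·t, the slope β becomes β/k and the residual variance does not change. For a 12-week arm difference in change of D:
- weeks: β = D/12
- waves 0–3: β = D/3
- 0–1 over follow-up: β = D

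For D = 0.8 residual SD the stated ratio is 0.067, 0.267 and 0.80. The fit and the test statistic are the same in each case.

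**3. Denominator.** Residual SD / total SD = √(1 − r), so dividing by the residual SD inflates by 1/√(1 − r).
- r = .638: √0.362 = 0.602; inflation 1.66
- r = .742: √0.258 = 0.508; inflation 1.97

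**4. Both together.** Take a 12-week difference of d = 0.5 in total-SD units.

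| Time coding | Calculation | Ratio reported |
|---|---|---|
| Weeks | 0.5/12 × (1.66 to 1.97) | 0.07–0.08 |
| Waves | 0.5/3 × (1.66 to 1.97) | 0.28–0.33 |
| 0–1 over follow-up | 0.5 × (1.66 to 1.97) | 0.83–0.98 |

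None of the three returns 0.5. Read the other way, a ratio of 0.5 under wave coding means 3 × 0.5 = 1.5 residual SD over 12 weeks, which is d = 1.5/1.97 to 1.5/1.66, or 0.76 to 0.90.

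**5. Simulated fit.** Data for 2,000 people were generated with random intercept SD 1.4, random slope SD 0.2, residual SD 1 and a 12-week arm difference of 0.8. The mixed model gave a ratio of 0.276 in waves and 0.828 on 0–1 coding, with the same residual SD (0.99) and the same test statistic (12.34). The arm difference at the last wave divided by the baseline SD was 0.46. The weekly-coded fit did not converge properly and was set aside; the weekly figures above come from the exact rescaling in step 2.

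**The case against.** Several points on the other side have force.

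- **Time coding is analysis-plan detail.** In a condensed article, an unstated unit of time is not in itself a fault, and step 1 hints at waves. This stands. It does not rescue the rule, because no time coding turns the residual SD into the SD that Cohen's d uses.
- **The article claims only a similar reading to Cohen's d.** True, but it applies his exact cut-points.
- **A tempting stronger reading is that the same effect could be labelled negligible or large, and that the next trial could be sized at 36 to 48 people instead of 128.** Those totals are two-sample t-test sizes at 80% power for 0.98, 0.83 and 0.5. The article does not support this reading. Large needs time scaled 0–1 over follow-up, which nothing in the text suggests. Weeks against waves is a factor of 4, which cannot take a value from below 0.2 to 0.8 or more. With waves, 0.28–0.33 would imply about 290 to 400 people, an error in the opposite direction. Nor does the article say that these ratios will set a sample size.
- **The inflation factor is a proxy.** It rests on a rank correlation over 4 weeks in a 73-person pilot, for outcome expectations only. The article gives no such figure for intentions, self-reported exercise or Fitbit data, and random slopes would change the factor. This stands for the size. The direction is less fragile: at an assumed r of 0.5 the inflation is still 1.41.
- **The secondary hypotheses are tested by p-values, which do not change.** This stands, and slopes in outcome units also remain valid.

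**Conclusion.** The effect-size rule is wrong as written. Its numerator is a slope per unit of time and its denominator is a within-person SD, so Cohen's cut-points do not apply to it.

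For outcome expectations the denominator inflates by about 1.7 to 2.0 times, while the slope deflates by 3 (waves) or 12 (weeks). With either of these codings the net effect is to understate: d = 0.5 reads as 0.28–0.33 or 0.07–0.08. Overstatement, to 0.83–0.98, arises only with 0–1 coding. These sizes rest on stability standing in for the within-person correlation and on compound symmetry. That the two scales differ does not depend on those figures.

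The consequence is limited to the reported strength of effect, its label, and any use of it in preparing the larger study. The slope tests, the recruitment and retention criteria and the primary feasibility aim are untouched, and the correct quantity can be computed from the same data. Severity is moderate.

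**What to change.** Replace the rule in section 3.3.2 with a definition that does not depend on time coding:

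- Standardised effect = model-estimated arm difference in change at 12 weeks (slope difference × length of follow-up, in the unit used for time) ÷ pooled baseline SD of that outcome, with a 95% CI.
- Apply the small, medium and large labels to that quantity only.
- Correct the mistyped phrase for the square root. Read literally, it would also allow division by the variance itself.

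Pooled baseline SD is one reasonable choice of standardiser. What matters is that a between-person SD and the time contrast are named before the analysis, so that the coding cannot choose the label.

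The cost is a sentence of plan wording and one line of code. No new data, design change or extra participants are needed. Reported effect sizes will change, upwards or downwards according to the coding that would have been used.
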